## Outcome measures

### Primary outcome measures

*Quality Function Measure (QFM)* is an observational criterion referenced measure designed to evaluate the quality of movement in standing and walking skills in CYPwCP.^68^ It is used in conjunction with the Gross Motor Function Measure (GMFM) using dimensions D and E, which focus on ‘standing’ and ‘walking, jumping and running skills’, which are considered proxy clinical gait measures. The GMFM is the ‘gold standard’ tool for evaluating gross motor function in CYPwCP, evaluating ‘how much’ of a gross motor skill a child can perform.^69^ However, there are concerns regarding GMFM’s sensitivity in capturing subtle yet meaningful change postintervention, due to ‘ceiling effects’ of the measure when used with ambulant CYPwCP in GMFCS levels I–III.^22 68 70^ The QFM scores movement quality and assesses ‘how well’ a child performs gross motor tasks.^68^ It has shown excellent rater and test–retest reliability (Intraclass correlation (ICC) 0.89–0.97). Minimal detectable change estimates (6%–9%) suggest that the scale has potential as an evaluative measure ([name], personal communication, 8 May 2018). However, to date, there are no published studies evaluating the responsiveness of QFM following BoNT-A injections.

In order to minimise bias, the video analyst will be blinded to the stage of treatment and assessment time point (ie, pre T_0_ or post T _1–3_ injection). To conceal these time points, each video containing GMFM D and E (standing and walking) dimensions is anonymised and randomly allocated a letter by a coworker not involved in the service. To minimise recall bias, a time lag will be built in of 2 weeks and videos of at least 10 other children will be scored before scoring the video of the same child at a different assessment time point. This is in keeping with previous QFM reliability studies that suggest a gap of 2 weeks before evaluating test–retest scores.^68 70^ Data will be entered into a secure database without access to previous scores until scoring for all assessment time points is complete.

*COPM* is a goal attainment tool modified for use in the paediatric population and frequently used in neurodisability research.^71–73^ It identifies concerns regarding ‘occupational performance issues’, that is, the ability to carry out functional tasks, allowing the identification of goals and has been used to document change post BoNT-A rehabilitation.^74^ In the paediatric population, areas of concern in a child’s self-care, activity and leisure are explored during the preassessment appointment with the clinical team. COPM has demonstrated high retest reliability (ICC 0.76–0.89), sensitivity to change and good content, construct and criterion validity for CYPwCP receiving BoNT-A.^75 76^ Families are asked to identify up to three areas of concern that they and their child hope to improve following lower limb BoNT-A injections. Whenever possible, goals are set with the child’s input.^77^ The child and parents are asked to rate their perception of both current performance and their satisfaction with this performance on a 1–10 ordinal scale. A score change of two or more points is considered clinically significant.^72 78^

### Secondary outcome measures

*Modified Tardieu Scale (MTS)* is a recognised clinical measure to differentiate dynamic spasticity from fixed contracture in a muscle. It determines the passive range of movement at two different movement velocities fast (R1) measuring dynamic muscle length and slow (R2) measuring static muscle length, with the relative difference between the two (R2–R1) determining the dynamic tone component of the muscle contracture.^79 80^ It is measured in degrees with a universal goniometer using standardised testing positions for each muscle. It has been postulated that the larger the dynamic tone component, the more amenable it is to treatment with BoNT-A.^78^ It is more effective than the Modified Ashworth Scale in identifying the presence of spasticity (88.9%, kappa=0.73, p=0.000) and the presence of contracture (77.8%, kappa=0.503, p=008).

*Faces Pain Scale* is a self-report measure of pain intensity developed for children, which has been shown to have good psychometric properties for pain reporting (modified for use by carer when the child is unable to self-report). The scale shows a close linear relationship with visual analogue scales. It is measured by an ordinal scale from 0 to 10 with pictorial representation of faces. A change score of 2 or more is said to be clinically significant.^81^

*Selective Motor Control* is a good discriminator of selective motor control and assesses a child’s ability to voluntarily and selectively control the dorsiflexors of the ankle.^77^ It is measured by an ordinal scale between 0 and 4. Higher score indicates better selectivity, inter-rater agreement has been shown to be moderate to good (kappa=0.58–0.77) with strong test–retest reliability (kappa=0.88–1).^79 82^

*One Minute Fast Walk Test* has been chosen as a proxy gait measure and is a good discriminator of functional ability for dynamic balance, muscle performance and endurance.^83^ Participants walk for 1 min along a 9 m corridor at maximum speed without running. They are able to use their usual walking aids and orthoses. Distance is calculated to the nearest 10 cm. It shows concurrent validity with the GMFM, with significant correlation between GMFM score and distance walked (r=0.92) and good reliability (ICC: 0.97).^84^

*Modified Timed Up and Go* is a good discriminator of balance, anticipatory postural control and functional mobility in CYPwCP. Participants are timed rising from a chair, walking 3 m to touch a star on the wall and returning to sit down as quickly as they can without running. Participants are able to use their usual walking aids and orthoses. The measure differentiates performance between CYPwCP at GMFCS levels I–III. It has shown excellent inter-rater reliability (ICC 0.83–0.99)^85^

*Participation Environment Measure – Child and Youth (PEM-CY)* is an innovative parent-reported participation measure for use with CYP between 4 and 18 years. It measures CYPwCP’s participation at home (10 items), school (5 items) and community (10 items), taking into account the environmental challenges within each setting. Summary scores for participation frequency, child’s involvement and parental desire for change are calculated for all domains. PEM-CY has demonstrated good internal consistency (ICC 0.72–0.83) and test–retest reliability (ICC 0.76–0.89).^86^

*Cerebral Palsy Quality of Life Measure (CPQOL)* is an HRQoL assessment administered by questionnaire, specifically designed for CYPwCP. It quantifies ‘well-being’ across seven key HRQoL domains. Items are scored on a nine-point rating scale, then summed and averaged to generate seven domain scores. There are two child-reported (CPQOL-Child: 9–12 years and CPQOL-Teen: 13–18 years) and two proxy-reported versions dependent on child’s age and cognitive ability (CPQOL-Child Primary caregiver: 4–12 years and CPQOL-Teen Primary care giver: 13–18 years). The questionnaire designers have stipulated a minimum age of 9 years for child self-reporting, however significant disagreement has been reported between child and parent proxy reports in many HRQoL instruments, and the child’s perspective will be sought whenever possible in this study.^87^ The CPQOL has demonstrated good internal consistency (child ICC 0.74–0.92; teen 0.81–0.96) and adequate test–retest reliability (child ICC 0.76–0.89; teen 0.59–0.83).^88 89^

### Semistructured interviews

Interviews will be used to elicit CYPwCP and parent/carers views of change following BoNT-A treatment. These are expected to last 60 min for parents and up to 30 min for children and will take place at home or in the hospital (depending on family preference). Interviews will be guided by a predetermined interview schedule, which will explore perceived change across all ICF domains to facilitate comparison with quantitative outcome measures, as well as investigate the acceptability of the standardised outcome measures used inphase 1 of the study. Parents will be interviewed separately from CYPwCP, although individual preference for parents to be present or absent during interviews with their child will be respected. Interviews with CYPwCP will be tailored to their age, cognitive and communication ability using a variety of different techniques, including art-based activities. Offering a toolkit of different creative techniques will ensure that the activities will be accessible to all CYPwCP involved in the interviews, acknowledging their different skills and personalities and their cognitive and physical abilities that is particularly important in this population of CYP.^90^ To ensure a representative sample of participants for phase 2, CYPwCP with a good, moderate and poor response to toxin (determined by the clinical team at the 6-month assessment) within each GMFCS level (I–III) will be invited to take part in phase 2. All interviews will be audio recorded with permission from participants.

### Sample size

Phase 1: this study has been powered to detect a difference on one of the two primary outcome measures, the COPM. The sample size power calculation is based on anticipated change in the COPM goal performance at the primary end point T1 (6 weeks postintervention) after BoNT-A treatment. A change in score of 2 or more points on the performance scale of the COPM would be considered clinically meaningful.^72 78^ An earlier study of lower limb BoNT-A intramuscular injections yielded SD between 1.4 and 1.7 for COPM performance.^77^ Based on a conservative estimate using a mean change of two points on the COPM performance scale (power 0.8, two tailed, p<0.05), 36 participants (12 in each GMFCS level) are required. Allowing for attrition and missing data over a 12-month period, a total of 60 participants (20 in each GMFCS level) will be recruited for phase 1 of the study.

As there are no studies reporting Quality Function Measure (QFM)^68^ as a primary outcome measure following BoNT-A injections, no data exist to inform a power calculation. It is anticipated that the results from this study will provide power calculation data for use in future multicentre trials using QFM.

Phase 2: a sample size of approximately 15 CYPwCP (five from each of the GMFCS levels I–III) and their parent/carer is anticipated to be sufficient to reach thematic saturation for the qualitative element of the study.^91^

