## Methods

### Study design

This is a mixed methods study comprising of two phases:

Phase 1: to meet objectives 1 and 2, we will use a prospective longitudinal study using a one-group repeated measures design with each child acting as their own control.

Phase 2: to meet objective 3, we will conduct interviews with a subgroup of CYPwCP and parent/carers from phase 1 to elicit their experiences and views of change following BoNT-A treatment.

Using a convergent mixed methods approach, quantitative data from phase 1 will be synthesised with qualitative data from phase 2 in order to gain understanding of the impacts of BoNT-A treatment.^55 64^

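### The 36 children given as the requirement for 80% power are not what the stated inputs require for the cohort pre-post comparison (7 to 14); the basis of the 80% should be stated and the precision given as a range

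*Protocol article*

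**What the plan says.** All references are to the protocol article.

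- **Study design:** phase 1 is a "one-group repeated measures design with each child acting as their own control".
- **Sample size, powered quantity:** the "anticipated change in the COPM goal performance at the primary end point T1 (6 weeks postintervention").
- **Sample size, SD:** an earlier study "yielded SD between 1.4 and 1.7 for COPM performance". The calculation opens with "Based on a conservative estimate", without saying in what respect it is conservative.
- **Sample size, other inputs and result:** for "a mean change of two points on the COPM performance scale (power 0.8, two tailed, p<0.05), 36 participants (12 in each GMFCS level"), are required. Recruitment is set at 60 (20 per level) to allow for attrition and missing data.
- **Data analysis:** the primary outcomes are analysed with generalised estimating equations over the post-intervention time points. No test within a GMFCS level, and none between levels, is described for the COPM.

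The article does not say whether the SD is of scores or of change, which pre-post correlation was assumed, or whether the 80% applies to each level or to the whole cohort.

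**The concern.** With each child as own control, a mean change of 2 against an SD below 2 is a standardised effect above 1. A paired comparison of that size needs far fewer than 36 children, so 36 at 80% power does not look like the result of the calculation described.

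Too few children is not the problem. What is at stake is the meaning of the headline power statement. It ties 80% power to a 2-point change, which the protocol treats as clinically meaningful. A reader who takes it at face value will expect a significant result at T1 to reflect a change of roughly that size. At the actual sample size, a much smaller mean change will be significant.

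**Working it through.** **Inputs** (Sample size section): mean change 2; SD 1.4 to 1.7; two-sided alpha 0.05, z = 1.96; power 0.80, z = 0.84. Three GMFCS levels.

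**Step 1. Reproduce the 36.** Two routes give it, both with SD 1.7.

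- Unpaired two-group normal formula: n per group = 2 × (1.96 + 0.84)² × 1.7² / 2² = 11.34 (unrounded z values), rounded up to 12. Then 12 × 3 = 36.
- Paired normal formula within one level: n = ((1.96 + 0.84) × SD of change / 2)², where SD of change = SD of scores × √(2(1 − ρ)). With SD of scores 1.7 and ρ = 0, the SD of change is 1.7 × √2 = 2.40 and n = 11.34, rounded up to 12. Then 12 × 3 = 36.

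At ρ = 0 the two formulas are algebraically the same, so the number cannot show which was used.

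**Step 2. Requirement for the cohort comparison.** One paired t-test (noncentral t), 2 points, 80% power:

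| Reading of the SD | SD of change | n required | Power at n = 36 |
|---|---|---|---|
| SD of change, lower | 1.4 | 7 | above 99.9% |
| SD of change, upper | 1.7 | 8 | above 99.9% |
| SD of scores 1.7, ρ = 0 | 2.40 | 14 | 99.8% |

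For 36 to be the 80% requirement, the SD of change would have to be about 4.2, well outside what the quoted SDs allow.

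**Step 3. Per-level reading.** Power of a paired t-test for 2 points with 12 children:

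| Assumption | Power at n = 12 |
|---|---|
| SD of scores 1.7, ρ = 0 | 75% |
| SD of scores 1.7, ρ about 0.12 | 80% |
| SD of scores 1.7, ρ = 0.2 | 83% |
| SD of scores 1.7, ρ = 0.5 (same as SD of change 1.7) | 96% |
| SD of change 1.4 | 99.4% |

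So about 80% per level is attainable, but only if 1.7 is an SD of scores and the pre-post correlation is close to zero.

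**Step 4. What the sample can detect.** Mean change detectable with 80% power (paired t), and the smallest observed mean change with p<0.05 in 36 children, t(0.975, 35) × SD of change / √36 with t = 2.03:

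| SD of change | Detectable, n = 36 | Detectable, n = 12 | Just significant, n = 36 |
|---|---|---|---|
| 1.4 | 0.67 | 1.24 | 2.03 × 1.4 / 6 = 0.47 |
| 1.7 | 0.82 | 1.51 | 2.03 × 1.7 / 6 = 0.58 |
| 2.40 | 1.15 | 2.14 | 2.03 × 2.40 / 6 = 0.81 |

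In 36 children, significance is reached at about 24% to 41% of the 2-point threshold (0.47/2 to 0.81/2).

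**The case against.** The strongest defence is the per-level reading. The article gives the requirement and the recruitment target by GMFCS level, quotes the SD for COPM performance rather than for change, and calls the estimate conservative. Taking 1.7 as an SD of scores with zero correlation fits all three and gives 12 per level. This stands as a possible origin of the number.

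Two stronger readings are therefore not supported. A reader might infer that an unpaired two-group formula was wrongly applied; Step 1 shows that a paired formula gives the same 12. A reader might also infer that the stated power is simply wrong; read per level, it is about right under those assumptions. Nor is the COPM comparison underpowered on any reading for the cohort.

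The defence does not clear the text, however. It needs three things that the article does not state: the type of SD, near-zero correlation, and 80% applying within each level. Near-zero correlation gives up the gain from using each child as own control. It also sits uneasily with the COPM retest ICC of 0.76 to 0.89 under Primary outcome measures, although retest reliability is not the correlation across a treatment. And no per-level test is described for the 80% to belong to.

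It is also fair to say that powering a test against zero at the clinically important difference is conventional, that the protocol names its 2-point threshold repeatedly, and that the sample serves other aims, such as predictors of response. These are reasons to keep N. A condensed article may leave the formula and correlation to the full protocol, but here the printed sentence itself links 36, 80% and 2 points in a way the described comparison does not bear out.

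**Conclusion.** The point holds in a limited form. For the one-group pre-post comparison that the article describes, its inputs require 7 to 8 children (SD of change 1.4 to 1.7), or 14 if 1.7 is an SD of scores with zero correlation, not 36; power at 36 is at least 99.8%. The number 36 is 12 per level times three, and the 80% belongs to a comparison that the described analysis does not contain.

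This rests on a paired t-test standing in for the T0 to T1 contrast of the estimating-equations model, on a pre-post correlation not below zero, and on the quoted SDs applying to this cohort. Which SD was quoted cannot be settled from the article, so every detectable-change figure is a range.

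The sample is ample for the COPM at T1. The statement of what it is powered for should be corrected, and the cost of leaving it is a likely over-reading of a small significant change. This is a correction of wording, not a threat to the validity of the study.

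**What to change.** Keep N at 36 evaluable and 60 recruited, and change the Sample size text:

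1. State whether the 80% applies within each GMFCS level or to the whole cohort. If per level, describe the per-level analysis; if cohort, drop 36 as the 80% requirement.
2. State whether 1.4 to 1.7 is the SD of scores or of change and, if of scores, the pre-post correlation assumed.
3. Restate the precision as a range. For example: 36 evaluable children give 80% power for a mean T0 to T1 change of about 0.7 to 0.8 points (SD of change 1.4 to 1.7), or 1.15 points if the SD of change is 2.40; 12 children in one level give 80% power for about 1.2 to 1.5 points, or 2.1 points. Once the type of SD is confirmed, keep only the figures that apply.
4. Add that clinical meaning will be judged by the 95% confidence interval of the mean change against 2 points, and by the proportion of children changing by 2 or more points with its confidence interval, rather than by p<0.05 against zero.

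The cost is a few sentences in the protocol or analysis plan. No extra children, visits or data are needed.

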**Figure 4 F4:**
[figure not shown]
Braun and Clarke’s six-step approach to thematic analysis.

### Participant and data management

Electronic data will be managed through a secure database held in GOSH. Participants will be allocated an identification code that will be used to deidentify their files and forms. Pseudonyms will be used in all reports and publications, and direct quotations will be anonymised. Paper documents and other manual files will be appropriately filed and stored securely in a locked filing cabinet at GOSH. Demographic information and consent forms will be stored separately to research data. Classification measures, child demographics and related information will be taken prior to baseline for the purposes of stratification and description of the sample. Audio and visual recordings will be uploaded onto secure password-protected encrypted National Health Service computers and deleted from the recording device immediately after uploading. This protocol has been reviewed and approved by the Research and Development team and Caldecott Guardian at GOSH.

### Patient and public involvement

Children and young people with CP and their parents have been involved in the development of this project, exploring the importance of the research, the appropriateness of the research questions, the acceptability of the research methods and best methods for disseminating findings. Fifteen ambulant CYPwCP receiving BoNT-A treatment at GOSH and their parents were consulted individually. A wider population of CYPwCP and their parents were also consulted via the SCOPE website and the advisory groups for CYPwCP at Brunel University and Young People’s Advisory Group at GOSH.

### Reference group/steering group

Three parents (all mothers) and three CYPwCP (two boys and one girl (not participants)) continue advising on the study through membership of the study steering group (parents) or reference group (CYP). Three professionals (two physiotherapists and one doctor) are also part of the steering group. By including CYPwCP and families perspectives together with regular contributions from practising clinicians within the service, we hope to ensure the inclusion of important values and preferences from families and clinicians alike, ensuring that the findings of the study remain relevant and applicable to the management of ambulant CYPwCP.^24 93 94^

## Discussion

This paper presents the protocol for a novel pragmatic prospective longitudinal observational study of BoNT-A use in ambulant CYPwCP at an established tertiary children’s centre in the UK. It will measure outcomes across all domains of the ICF and HRQoL over a 12-month period to observe change and examine factors associated with positive or negative response to lower limb BoNT-A injections. The introduction of a standardised outcome measure, QFM, to evaluate any change in movement quality following BoNT-A treatment will further inform exploration of the relationship between tone reduction and changes in activity, as well as any influence on participation and HRQoL for our cohort of CYPwCP. Mixed methods research designs are considered by many to be essential in the study of therapeutic interventions in CP.^55^ Including qualitative study data will ensure that the experiences of CYPwCP following BoNT-A injections are elucidated, considered and further understood.

This study, by identifying patterns of response to BoNT-A injections in key aspects of health across all the ICF domains, will provide clinicians and families with meaningful information to inform future treatment planning and optimise the use of BoNT-A in CYPwCP. Evidence will be generated about the appropriateness of the outcome measures used in detecting meaningful change after BoNT-A injections as well as their acceptability to CYP. In addition, the relationship between the standardised outcome measures used to capture treatment effect and the perception of outcome by children and their families will be investigated.

The results of this study will assist in the development of a pragmatic set of standardised clinical outcome measures (recognising minimum clinically important differences) in order to evaluate the effects of BoNT-A treatment in this cohort of patients. We hope this work will inform future evaluative research; working towards closer consensus on patient selection, injection frequency and consideration of how long treatment should continue, in order to assess the value of long-term use of BoNT-A treatment and its role in the management of CYPwCP.

A dissemination strategy has been devised to ensure the findings of this research are made widely accessible to families and professionals in order to maximise impact on the care of CYPwCP. Working in partnership with parent groups will strengthen our dissemination strategy, ensuring findings are shared in a variety of accessible formats reaching a wide range of families, professionals, as well as academics and policy makers helping ensure the findings are translated into practice. We will disseminate the results of the study through international peer-reviewed journals and at national and international conferences. A social media strategy will also be developed to ensure dissemination of a plain language summary of findings.
